#### Methods for any additional analyses (e.g. subgroup and sensitivity analyses) {27d}

N/A. Other than the above-mentioned (sensitivity) analyses, no additional analyses are planned.

## Methods: Monitoring

### Data monitoring committee

#### Composition of data monitoring committee (DMC) {28a}

N/A. A data monitoring committee is unwarranted for the purposes of this study, as no additional risk of harm is anticipated for participation. Moreover, no periodic data monitoring is carried out, except for the recruitment and inclusion progress performed by the TSC.

#### Explanation of any interim analyses and stopping guidelines {28b}

N/A. No interim analyses are specified, as no additional risks are expected for participation in the current trial.

### Trial monitoring {29}

Trial conduct is audited in multiple ways. Firstly, both the Medical Ethical Research Commission (METC Brabant) and the funder of the study (Foundation for VCVGZ Support) will be informed about the progress of the trial on a yearly basis by the PI. Secondly, the quality of collected data in CASTOR EDC is guaranteed through its integrated audit trail and will be assessed shortly after the start of data collection by the data manager. Thirdly, multiple participating institutes (Arkin NPI, GGZ De Viersprong, GGZ Oost Brabant) are subject to an internal and external independent audit cycle, in accordance with NEN-EN 15224, to ensure the quality of their TOP Clinical Psychiatric Care, specialist diagnostic research and treatment programs for people with complex psychiatric problems and PDs. Lastly, the trial steering committee has monthly meetings to oversee the trial conduct.

## Ethics

### Research ethics approval {30}

Ethical approval for P-DAET was issued by the METC Brabant (NL86263.028.24). Moreover, a data protection impact assessment (DPIA; TSB_1632) was conducted by Tilburg University’s Ethics and Review Board. Additionally, permission was sought from the participating institutions’ advisory committees of scientific research. Finally, all participants will provide written informed consent.

### Protocol amendments {31}

Any (non)substantial amendments to the study protocol will be reported to and ratified by the METC Brabant and reported publicly on clinicaltrials.gov. Further, the METC Brabant can impose follow-up steps after amendments.

### Consent or assent

#### Who will obtain informed consent {32a}

After eligibility screening, patients are informed by research staff both verbally and in writing. After at least a week, to ensure sufficient time for consideration, an informed consent appointment is planned either at a research site or via video conference. During this appointment, the prospect’s questions are discussed and, if applicable, the consent form is signed digitally or in writing by the prospect. Consent forms that are signed on paper at home during a video call conference are sent back by participants via conventional letter mail. Once received, the researcher or their representative signs the form, after which it is stored in a decentralised manner, and a copy is provided to the participant. The model consent form in Dutch is available upon request from the corresponding author.

#### Additional consent provisions for ancillary studies {32b}

The consent form specifically seeks permission for the use of participants’ data in ancillary studies and recruitment for follow-up studies. Prospects can still participate in the current study if they decline participation in ancillary or follow-up studies.

### Confidentiality {33}

During recruitment, eligibility screening, data collection, and archival, personally identifiable data is collected within the institutions from electronic patient files and securely stored at each participating institution in a separate linking file. In the linking file, each participant is linked to a pseudonym, meaning an application number or a study ID, depending on the time point (i.e. before or after inclusion). During recruitment, application, and eligibility screening, application numbers are used to communicate about participants. Signed informed consent forms are also stored in a decentralised manner at each participating institution. Access to both the linking files and consent forms is restricted to local research staff members who require it for their work, as well as any relevant supervisory authorities. After informed consent is obtained, a study ID is generated, enabling pseudonymized central data collection in CASTOR EDC. If an application does not lead to participation, all personally identifiable data is removed from the linking file, except for the original electronic patient file number and the application number. Linking files are retained at the participating institutions for 15 years after study completion, while pseudonymized research data is archived in CASTOR EDC for 15 years and in TiU Dataverse indefinitely (see *Data Management {26}*).

### Ancillary and post-trial care {34}

The studied interventions are standard treatments within the participating Dutch mental healthcare institution. Therefore, participation does not involve additional risks, and therapeutic progress is reviewed collaboratively between the participant and therapist throughout the treatment. After completing the allocated treatment, participants can seek follow-up care if desired. However, the participant’s respective institution is not allowed to provide care of the opposite treatment arm for the duration of the trial, unless explicit permission is sought and obtained from the TSC. Dropping out of the study will not affect the treatment provided. If participants discontinue the allocated treatment, they will still be assessed and included in the analysis according to the intention-to-treat principle, unless consent is withdrawn.

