### Sample size {19}

The required sample size was determined using a computer simulation. Twenty-one thousand datasets with varying sample sizes were simulated for an RCT design with seven repeated measurements on a continuous outcome variable, where both interventions exhibit equal improvement over time. The outcome measures were assumed to follow a multivariate normal distribution in both groups, with a repeated measures correlation of 0.50 and a decrease of *d* = 0.30 in both groups across the seven repeated measurements. Each of these datasets was analysed using a longitudinal multilevel model (see *Statistical methods for primary and secondary outcomes, including harms {27a}).* Subsequently, in each dataset, it was tested whether generalist treatment is non-inferior to specialist treatment by examining whether the lower limit of the two-sided 95% confidence interval of the difference between treatments in improvement over time is greater than the non-inferiority limit of *d* = 0.25. It was found that with this design, 316 participants are necessary (158 per group) to test non-inferiority with a power of 0.80 and α = 0.025. To account for attrition, which we estimate at 11.7% for the primary endpoint (T4) based on a similar study [19], the complete sample needs to consist of (316/0.883 = 357.87) 358 participants. This comes down to 179 participants per treatment condition.

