### Blinding

#### Who will be blinded {24a}

Treatment providers and participants cannot be blinded due to the nature of the interventions, e.g. containing psychoeducation directly related to and explained within the framework of the intervention, leading to automatic unblinding of participants. Understandably, therapists are unequivocally aware of the intervention type they are applying. Appointments for the STiP-5.1 outcome assessments will be scheduled by unblinded research staff members for blinded research staff. Participants are asked not to disclose their allocation during the appointment. Thus, staff members administering the interview at post-treatment and follow-up timepoints will be blinded. This is further ensured through CASTOR EDC roles and permissions functions.

When data is exported from CASTOR EDC, an unblinded data manager will pseudonymise the conditions. Afterwards, the data is processed, analysed, and interpreted by blinded data managers, statisticians, junior researchers, and conclusion makers. The pseudonymisation of the data will only be undone after conclusions are drafted. In this way, statisticians and conclusion makers are ensured to be blinded. The junior researchers are not blinded during data collection to enable effective day-to-day management of the trial.

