#### Plans to Promote Participant Retention and Complete Follow-Up {25b}

Participant retention is promoted through multiple strategies aimed at a personalised approach that minimises burdens and maximises accessibility [114, 115]. Whenever possible, existing data is reused to avoid redundant assessments. For example, STiP-5.1 interviews conducted during regular intake are repurposed for eligibility assessment and baseline measurements. Routine outcome monitoring (ROM) is adapted to prevent overlap with study instruments and again supplemented with SIPP-SF and BSI results at designated time points to facilitate usage during treatment trajectories. Before each assessment, research staff call participants to discuss their availability and preferred mode of completion (online or in-person), ensuring a participant-centred approach. Online assessment is set as the default to enhance convenience. Furthermore, participants receive a total reimbursement of €50, distributed across T1 (€15), T4 (€20), and T6 (€15). If a participant considers dropping out, research staff will encourage continued participation by offering a reduced test battery focused on collecting the primary outcomes at T4 and T6. The extent of this set depends on the participant’s willingness.

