#### Definition of analysis population {27b}

Following the intention-to-treat principle, participants will be analysed according to the assigned intervention arm, disregarding actual compliance with the assigned intervention. Furthermore, in inspecting the robustness of the noninferiority outcomes, supportive sensitivity analyses are carried out per-protocol, meaning only participants who did not drop out of the assigned intervention are included.

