#### How missing data will be handled in the analysis {27c}

The multi-level mixed-effects models allow for incomplete outcome data, while assuming Missing at Random (MAR). The actual missingness mechanism is, however, unknown. This will be examined by comparing baseline characteristics between participants with and without missing outcome values. Furthermore, to examine the influence of missingness on the primary analyses, two sensitivity analyses are performed; the first repetition of the primary analyses will additionally use multiple imputation through predictive mean matching to impute the missing values on the repeated measurements of the dependent variable. The second repetition will cover a complete case analysis, including only the participants without missing data on the respective primary outcome.

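### Read literally, the care section takes participants who withdraw consent out of the intention-to-treat analysis, an exception that the analysis-population section does not make (minor)

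*Protocol article*

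**What the plan says.** Three sections bear on who is analysed.

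- **Ancillary and post-trial care {34}**, on participants who discontinue the allocated treatment: "they will still be assessed and included in the analysis according to the intention-to-treat principle, unless consent is withdrawn".
- **Definition of analysis population {27b}**: "participants will be analysed according to the assigned intervention arm, disregarding actual compliance with the assigned intervention". The only departure it disregards is non-compliance, and it makes no exception for withdrawn consent.
- **How missing data will be handled {27c}**: "The multi-level mixed-effects models allow for incomplete outcome data, while assuming Missing at Random (MAR"). It adds two sensitivity analyses of the primary models, one with multiple imputation and one with complete cases.

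The surrounding design also matters. Under Who will be blinded {24a}, "Treatment providers and participants cannot be blinded due to the nature of the interventions", while for the STiP-5.1 "staff members administering the interview at post-treatment and follow-up timepoints will be blinded". Someone considering dropping out is encouraged to stay by "offering a reduced test battery focused on collecting the primary outcomes at T4 and T6". The statistical methods section {27a} puts two STiP-5.1 time points and five LPFS-BF 2.0 time points into the T4 models, with three and seven respectively in the T6 models. The LPFS-BF 2.0 is formally tested only if the STiP-5.1 shows non-inferiority.

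**The concern.** In {34} a single exception governs two verbs, being assessed and being included in the analysis. If it meant only that assessment stops, inclusion would need no exception, because the model in {27c} already accepts a participant whose series breaks off. So {34} and {27b} describe different analysis sets, and two analysts could build different datasets once it is known who withdrew.

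The MAR argument depends on earlier scores staying in the model, since they carry the information about the later missing ones. Removing the whole participant turns missing follow-up into a post-randomisation exclusion. Neither sensitivity analysis in {27c} clearly brings such a participant back, and the per-protocol analysis excludes more people. Participants know their arm, so the decision to withdraw may depend on arm and progress. Blinded interviewers protect the rating, not that decision. If poorly responding generalist participants withdrew more often than their specialist counterparts, excluding them would move the estimate towards non-inferiority.

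**Working it through.** **1. The plan's own figures.** Sample size {19} states "316 participants are necessary (158 per group) to test non-inferiority with a power of 0.80", with 11.7% attrition at T4: 316 / (1 − 0.117) = 357.87, hence 358, or 179 per arm. This reproduces. The 316 came from simulation. A linear-trend approximation (seven measurements, correlation 0.50, margin 0.25, one-sided α 0.025) gives 324 in total for equally spaced times and 302 for the actual visit months, so 316 is plausible. The section prints the limit without its sign ("is greater than the non-inferiority limit of *d* = 0.25"). I take it as −0.25, as in the objectives. Consent withdrawal is not separated from other attrition.

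**2. What literal application would remove.**

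| Time of withdrawal | STiP-5.1 (T0, T4 in the T4 model) | LPFS-BF 2.0 (five points to T4) and other repeated secondary scores |
|---|---|---|
| Before T4 | Baseline only, so essentially no information on the treatment effect | All scores collected before withdrawal |
| Between T4 and T6 | An observed, blinded T4 score | All scores collected, including T4 |

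**3. Size of the shift.** Let w_G and w_S be the proportions withdrawing and excluded in the generalist and specialist arms. Let withdrawers be D SD worse than those who stay. Exclusion raises an arm's mean by w × D, so

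bias in favour of generalist treatment = (w_G − w_S) × D.

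The rates and D are assumptions, as the article gives none.

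| w_G vs w_S | D = 0.25 | D = 0.5 | D = 1.0 | Share of margin |
|---|---|---|---|---|
| 5% vs 5% | 0 | 0 | 0 | 0% |
| 5% vs 2% | 0.0075 | 0.015 | 0.03 | 3–12% |
| 10% vs 5% | 0.0125 | 0.025 | 0.05 | 5–20% |
| 11.7% vs 5% | 0.017 | 0.034 | 0.067 | 7–27% |

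Swapping the arms reverses the sign, for example −0.0125 to −0.05 for 5% vs 10%.

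**4. Effect on the error rate, STiP-5.1.** This applies only to withdrawal after T4 with the T4 score removed. With baseline adjustment, correlation 0.5 and 158 per arm, SE = √(2/158 × (1 − 0.5²)) = 0.0974. With the true difference at −0.25, non-inferiority is declared if the estimate exceeds −0.25 + 1.96 × 0.0974 = −0.059. The probability of that is 1 − Φ(1.96 − shift/0.0974):

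- shift 0: 2.5%
- shift 0.025: 4.4%
- shift 0.05: 7.4%

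Keeping the observed T4 scores gives no shift.

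**5. Effect on the LPFS-BF 2.0.** Simulation: 4,000 trials per scenario, 179 per arm, T0–T4, correlation 0.5, true T4 difference −0.25. Withdrawal after T3 is weighted towards poor T3 scores in the generalist arm and random in the specialist arm.

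| Withdrawal | Withdrawers excluded: mean estimate, false non-inferiority | T0–T3 kept: mean estimate, false non-inferiority |
|---|---|---|
| 8% vs 3% | −0.231, 4.0% | −0.250, 2.7% |
| 10% vs 4% | −0.227, 4.4% | −0.251, 2.4% |

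The gap between the two analyses is about 0.02 SD (0.250 − 0.231 = 0.019; 0.251 − 0.227 = 0.024). Making withdrawal outcome-related in one arm only is deliberately unfavourable.

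**The case against.** The strongest reply is that the clause is being over-read. It stands in a section on care, not on the analysis set, and concerns people who stop treatment. An exception for withdrawn consent is a common ethical provision and can mean simply that no further data enter. The sections that govern the analysis, {27b} and {27c}, point towards keeping what was collected. The fate of existing data is often settled in the full protocol and the consent form, neither of which is shown.

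Much of this stands. A reader might infer that the plan deletes outcomes already measured. It does not say so: no sentence orders removal of enrolled participants' data on withdrawal, and none says that they are kept. A reader might also infer that the trial's main conclusion is biased towards non-inferiority. The documents do not support that either. They give no withdrawal rate, no difference between arms and no link to outcome. The gatekeeping STiP-5.1 has almost nothing to lose from withdrawal before T4. Because the LPFS-BF 2.0 is tested only after the STiP-5.1 passes, its error rates above are not trial-level rates. Calling the trial open-label without qualification would overlook the blinded STiP-5.1 assessors. Formal withdrawal is probably only part of the projected 11.7% attrition, and the reduced battery should keep some would-be dropouts in.

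What does not stand is that nothing needs settling. The article does more than leave the matter open: it states an exception to inclusion in the analysis that its own population definition lacks.

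**Conclusion.** The point holds in a limited form, with minor severity. As worded, {34} excludes participants who withdraw consent from the intention-to-treat analysis, {27b} does not, and the MAR approach in {27c} is best served by keeping their earlier data. The consequence depends on how the clause is applied and on facts not yet known. Under full exclusion the shift is about 0.01 to 0.05 SD for an assumed 10% vs 5% withdrawal with D between 0.25 and 1.0. It is zero if withdrawal is alike in both arms, and works against non-inferiority if poorly responding specialist participants withdraw more. The false non-inferiority rates of 4.4% and 7.4% illustrate assumed shifts; they are not predictions. The sample size calculation is unaffected.

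**What to change.** Replace the closing exception in {34} and put the same rule in {27b}, for example: on withdrawal of consent no further data are collected; data collected up to that date stay in the analysis in the assigned arm; data are removed only where the participant explicitly asks for erasure or the signed consent form promises removal; and the number of such removals is reported by arm. At withdrawal, record whether the participant is stopping treatment, stopping assessments or refusing use of data, so that the three are not merged.

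The cost is one sentence in the protocol and, if needed, matching wording in the consent form for new participants. Promises in forms already signed must be honoured, so a few removals may remain. According to Trial status, enrolment is expected to run to December 2026 and data collection to December 2029, so the rule can be settled before outcomes are analysed.

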## Discussion

Although generalist treatments are widely used, the P-DAET trial is the first RCT assessing the non-inferiority of generalist treatment (GIT-PD) compared to specialist treatment (ST/MBT). We expect to find that, on average, generalist treatment is non-inferior to specialist treatment in terms of improving the level of personality functioning, general symptom severity and psychosocial functioning at post-treatment (18 months), as well as maintaining improvements at follow-up (30 months). Additionally, generalist treatment is expected to be more cost-effective than specialist treatment at both post-treatment and follow-up. Lastly, it is hypothesised that a combination of individual participant characteristics can predict differential treatment response above chance level, enabling the construction of a personalised treatment selection algorithm. P-DAET is, ultimately, aiming to contribute to the organisation of accessible and optimal allocation of cost-effective evidence-based psychotherapeutic care for those suffering from severe personality disorders by addressing these gaps in our current knowledge. The core clinical relevance of this study is determining whether a well-structured generalist treatment can serve as a non-inferior alternative to specialist treatment on average, while identifying which patients in particular require specialist care.

The study has several strong and innovative points. First, our study focuses on comparing treatment frameworks, rather than comparing specific treatment methods. Specifically, this study goes beyond comparing GIT-PD with MBT or ST: It operationalises the conditions needed for implementation and delivery of treatments (i.e. generalist vs. specialist), distinguishing them by the very factors that often hinder large-scale implementation of specialist treatments, referring to the required (and often costly) disciplinary mix, intensive training demands, level of specialisation and supervision, and the typically high dosage and duration of these treatments. By contrast, generalist treatments, including GIT-PD, are proposedly to be less hindered by these factors, as they require minimal additional resources beyond existing treatments-as-usual, while harnessing the common factors across PD treatments. This positions generalist treatments as substantially easier to implement, and therefore, as a potentially more accessible commodity to enhance the general level of care for individuals with severe PDs on a broader scale, compared to specialist treatment. The central question is whether this increased scalability comes at a cost. We hypothesise that, on average, it does not. However, for certain subgroups of patients—those with specific clinical profiles—specialist treatment may still be the preferred or necessary option. As such, this study aims to inform a more effective and equitable allocation of limited specialist resources, while contributing to more accessible and good-enough care for individuals with severe PDs.

Second, our study aligns with a dimensional diagnostic framework, both in specifying the target population and in evaluating treatment outcomes. Since the introduction of the Alternative Model for Personality Disorders (AMPD) over a decade ago [46], few clinical trials have adopted this framework as an outcome measure. P-DAET is among the first to do so [53]. Given the novelty of assessing impairments in self and interpersonal functioning as primary outcomes, we chose to integrate both clinician-rated and participant-reported perspectives. Each approach has distinct advantages: repeated administration of the STiP-5.1 interview allows for blinding of outcome assessors, thereby reducing potential bias [58], while being better able to capture latent PD severity than self-report measures [59]. However, its use in psychotherapy research is novel, making it unclear to what extent the measure is sensitive to change. In contrast, the LPFS-BF 2.0 questionnaire has demonstrated sensitivity to change in previous studies and is well-established in international research. It is also easy to administer repeatedly and imposes minimal burden on participants. Given these considerations, the STiP-5.1 interview will be prioritised in our primary outcome analysis, while the LPFS-BF 2.0 will supplement and contextualise findings to enhance interpretability, especially when the sensitivity to change of the STiP-5.1 appears to be insufficient. Another major strength of the present study is its inclusion of multiple relevant outcome domains, resulting in a comprehensive and clinically meaningful set of measures. These include impairments in self and interpersonal functioning, severity of traditional personality disorder (PD) symptoms, general psychiatric symptom severity, and psychosocial functioning. The integration of both more variable outcomes—such as PD symptom severity—and more stable outcomes—such as psychosocial functioning [125, 126]—is particularly valuable for capturing the broad range of clinically relevant consequences associated with severe PDs.

Still, any future results of the P-DAET trial must be interpreted within the context of potential limitations. Recently, it was argued that non-inferiority trials must feature an inactive control condition, as only then can the effectiveness of both active conditions be implied [127]. However, ethical concerns arise when considering an inactive condition, due to the long duration of treatments. With many patients already waiting extensively to start a PD treatment, sometimes for several years, randomisation of these patients to an inactive condition is deemed unfeasible and unethical. Moreover, we think that the inclusion of an inactive control condition is not necessary in the present study. The control condition—specialist psychotherapy—has consistently been shown to outperform inactive conditions across a wide range of studies employing diverse treatment methods. A substantial body of evidence demonstrates that treatment programs characterised by key features—such as a solid theoretical and methodological foundation, manualisation, delivery by well-trained professionals, and adequate dosage—are more effective than no treatment or unstructured treatment as usual [10–14]. Given this, we consider the effectiveness of specialist treatments sufficiently established, provided that they are delivered under conditions consistent with those shown to be effective in prior research. To address the potential concern that the specialist treatments in our study might not meet such standards, we have aimed to restrict inclusion to MBT and ST programs that conform to the specifications used in their respective randomised controlled trials. This includes adherence to established parameters regarding treatment duration, dosage, team composition, training requirements, format, content, and level of specialisation.

Another potential concern is the difference in average treatment duration between conditions. Indeed, treatment dosage and duration are among the defining distinctions between the generalist and specialist approaches. In line with previous trials, specialist treatments are expected to be delivered at a significantly higher dosage than the generalist condition. To ensure comparability between conditions, assessment time points are scheduled at fixed intervals, independent of treatment type. The primary endpoint is set at 18 months after treatment initiation, aligning with the projected average treatment duration for specialist treatments. While actual treatment durations may vary at the individual level, the intensive treatment phase is expected to be completed in all programs by this 18-month mark, with only low-intensity booster sessions continuing beyond this point. Therefore, the 24-month time point has been designated as the post-booster follow-up, by which time treatment trajectories in both conditions will have concluded for nearly all participants. This alignment of measurement time points ensures comparability in evaluating (cost-)effectiveness across conditions. Furthermore, the extended follow-up assessments at 24 and 30 months allow for the examination of potential delayed or sustained effects related to differences in treatment duration.

In conclusion, P-DAET will be the first randomised controlled trial to compare the non-inferiority of a generalist treatment approach (GIT-PD) directly to specialist treatments (MBT/ST) for individuals with severe personality disorders, as defined by the AMPD. This study is expected to generate novel insights into the effectiveness and real-world applicability of both generalist and specialist interventions. It will also address which patient needs are better met by more expensive specialist interventions. In this way, it contributes to a greater accessibility for all patients with severe personality disorders as well as an empirically supported assignment of these patients to different treatment types.

